#### **5.4.2.6 Withdrawal of a Subject as a Result of Occurrence of a Serious Adverse Event**

Follow-up visits will be carried out for all subjects who are withdrawn due to occurrence of an AE or in connection with a change in any other safety indicator (vital sign or clinical laboratory result).

If any subject develops an SAE leading to premature withdrawal, the event will be fully followed-up to resolution of the problem, to acknowledgement of the diagnosis of the SAE or to change in status of the acute SAE as chronic or stable or as long as such a change is justified from a clinical point of view. However, for premature withdrawal in connection with the emergence an SAE that is considered to be clinically relatively favorable (for example, the diagnosis is known, and it is expected to be resolved completely within a week), intermittent follow-up may be accepted as long as the plan for follow-up of the event is fully described in the notes section of the subject's CRF.

### **5.4.3 Handling of Withdrawals**

In case of premature withdrawal for any reason, the investigator should exert his/her best effort to:

- 
- Conduct an interview to determine if the subject has had any reaction or AE (serious or non-serious) during the period one month after any study vaccination that has led to the withdrawal. Where possible, the investigator should visibly or physically assess any reported adverse reaction or AE.
  - Attempt to complete all scheduled procedures and evaluations planned for a) Day 28 (exclusive of administration of study vaccine or placebo) if premature withdrawal occurs prior to Day 28 but after administration of dose one of study vaccine or placebo or b) Day 56 if premature withdrawal occurs prior to Day 56 but after administration of dose two of study vaccine or placebo.
  - Document the reason for premature withdrawal on the CRF.

The trial Sponsor and PVS must be informed within 24 hours about all instances of the premature termination of a volunteer's participation in the trial. Any withdrawal that occurs while a subject is scheduled to be in the isolation unit requires immediate notification to the Sponsor and PVS. While participation in the trial is voluntary and subjects are free to withdraw consent at any time, subjects will be told that local public health authorities might be notified of any subject's premature exiting from the isolation unit. An SOP for the isolation unit will detail procedures to be followed for any withdrawal that occurs while a subject is scheduled to be in the isolation unit.

Withdrawal of a subject *by the investigator* may occur only if the subject is identified to have one of the listed exclusion criteria or if continued participation of the subject threatens the subject's well-being or the integrity of the study (or the well-being of other subjects in the isolation unit). After administration of dose one (or dose two) of study vaccine, a subject who is scheduled to be in the isolation unit may be withdrawn *by the investigator* only if the subject develops a reaction to study vaccine which the investigator believes threatens the subject's well-being; the withdrawn subject must be treated or transferred to a treatment facility.

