### **3.2 Study Outcome Measures**

#### **3.2.1 Primary Outcome Measures**

The safety profile will be parameterized as the proportion of subjects experiencing adverse events (AEs) of the following four categories:

- 
- Immediate reactions occurring within two hours of administration of any dose, measured as observed by study staff or reported by the subject to study staff.
  - Adverse events commonly associated with intranasal vaccination (solicited local and systemic reactions) occurring greater than two hours after administration of any dose of study vaccine or placebo through 7 days following any dose, measured as observed by study staff or reported by the subject to study staff.
  - All other adverse events (including unsolicited events) occurring during the 7 days following any dose, measured as observed by study staff or reported by the subject to study staff. This includes abnormal laboratory findings from blood and urine specimens collected on Days 7 and 35.
  - All serious adverse events (SAEs) occurring within 4 weeks of receipt of any dose, as observed by study staff, reported by the subject to study staff, or noted by the subject on a diary card. This includes abnormal laboratory findings from blood and urine specimens collected on Days 28 (pre-vaccination) and 56.

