#### **5.4.2.5 Withdrawal of a Subject as a Result of Withdrawal of Informed Consent**

If a subject wishes to withdraw consent for participation in the trial after the subject has been admitted to the isolation unit and has been administered dose one or dose two of study vaccine or placebo, the subject will be requested to complete evaluations for that day and to complete either Day 28 or Day 56 evaluations, as applicable. Besides, to ensure safety any subject exhibiting influenza virus shedding in a nasal swab specimen will remain in the isolation unit for a more prolonged period until results confirming that no influenza virus is detected in a nasal swab for at least two consecutive days are obtained.

If possible, the subject should indicate the reasons for the termination of participation. The subject will be informed that the public health authorities will be notified of the subject's premature discharge from the isolation unit, as well as of the results of rRT-PCR testing of the subject's nasal swab specimens for detection of viral shedding. The subject will be advised to remain at home and avoid close contact with other persons until 7 days post-administration of study vaccine or placebo have passed.

If a subject wishes to withdrawal consent for participation in the trial after the subject has been discharged from the isolation unit, the subject will be requested to return the self-observation diary card and complete either Day 28 or Day 56 evaluations, as applicable. If possible, the subject should indicate the reasons for the termination of participation.

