7. Subjects will be given a diary card in which they will be asked to record any local and/or systemic reactions that might appear from Days 7 (after discharge from the isolation unit) to Day 28 (Day 28 being the scheduled day of readmission to the isolation unit for dose two of study vaccine or placebo) and to record any concomitant medications. Subjects will be instructed how to use the diary card on this day. All relevant explanations should be included in the diary card. The diary card will also have contact information for the investigators, should the subject have any questions.
8. The subject will be instructed that if the subject later experiences an AE requiring medical care, the subject should inform the investigator as soon as possible and seek medical care as appropriate. If the subject visits a health care provider, the subject should be sure to inform the health care providers of participation in this study and provide the provider with contact information for the investigator.
9. If the subject's Day 6 and Day 7 nasal swab specimens are influenza A negative by rRT-PCR, the subject will be discharged from the isolation unit and informed of the scheduled date of return to the unit.

---

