**7.2.10 Day of Second Admission into the Isolation Unit (Day 28)**

1. Subjects must present to the study center by 08:00. Study staff will confirm subject identity.
2. Study staff will review subject diary cards and interim histories with the subject and inquire about any new medical events since medical histories were last updated.
3. Blood specimens will be collected for testing a CMP and a CBC with differential. Specimen collection information must be documented on the CRF and in specimen collection logs.
4. A urine specimen will be collected for urinalysis testing via dipstick. Specimen collection information must be documented on the CRF and in specimen collection logs. For women only, the urine specimen will be collected for pregnancy testing. Any out-of-normal-range result will be recorded as an AE and discussed with the investigator to determine continued eligibility for dose two of study vaccine or placebo.
5. While blood specimens are being tested, a study clinician will perform a physical examination and record the information on the CRF. Results will be reviewed by study staff and with the subject and any AEs that have occurred will be recorded in the appropriate section(s) of the CRF.
6. A study otolaryngologist will perform an ENT examination and record the information on the CRF. Results will be reviewed by study staff and with the subject and any AEs that have occurred will be recorded in the appropriate section(s) of the CRF.
7. Upon receipt of results of CMP and CBC with differential testing, results will be reviewed by study staff and with the subject. Any out-of-normal-range result will be recorded as an AE and discussed with the investigator to determine continued eligibility for dose two of study vaccine or placebo.
8. If continued eligibility is confirmed, a study clinician will again review the procedures for the vaccination study and admission into the isolation unit. Continued informed consent will be confirmed and the subject admitted into the isolation unit. Upon admission into the isolation unit, a subject may proceed to undergo procedures related to administration of study vaccine or placebo and evaluation of vaccine safety and immunogenicity.

If the subject is no longer eligible for receipt of dose two of study vaccine or placebo, the investigator should not admit the subject into the isolation unit but should conduct steps 9 and 10, below, prior to withdrawing the subject from the study.

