4=Life threatening: any adverse experience that places the subject, in the view of the investigator, at immediate risk of death from the reaction *as it occurred*. (The investigator should *not* grade a reaction as life-threatening that had it occurred in a more severe form, might have caused death.)

For fever, as measured by axillary body temperature, the grading scale will be as follows:

|                     |                  |
|---------------------|------------------|
| 0=none:             | <37°C            |
| 1=mild:             | 37°C to 37.5°C   |
| 2=moderate:         | 37.6°C to 38.5°C |
| 3=severe:           | 38.6°C to 40°C   |
| 4=life threatening: | >40°C            |

Changes in the severity of an AE should be documented to allow an assessment of the duration of the event at each level of intensity to be performed. AEs characterized as intermittent require documentation of onset and duration of each episode.

**Relationship to Study Vaccines:** The clinician's assessment of an AE's relationship to study vaccine is part of the documentation process, but it is not a factor in determining what is or is not recorded in the study. If there is any doubt as to whether a clinical observation is an AE, the event should be recorded. All AEs must have their relationship to study vaccine assessed using the terms "related" or "not related." To help assess, the following guidelines will be used:

Related – There is a reasonable possibility that the study vaccine caused the AE. Reasonable possibility means that there is evidence to suggest a causal relationship between the study vaccine and the AE.

Not Related – There is not a reasonable possibility that the administration of the study vaccine caused the event.

All solicited and unsolicited AEs occurring during the study will be assessed and recorded. For clarity, unsolicited events includes those observed by study staff while the subject in admitted to the isolation unit and all AEs either recorded by the subject on diary card or reported by the subject during review of interim medical histories or clinical examinations.

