### **11.2 Definition of Analysis Sets**

All primary safety descriptions and summaries will be performed on an intention-to-treat basis. Supportive per-protocol analyses will also be conducted on all enrolled participants who are randomized, receive two doses of study vaccines and complete the Day 56 visit.

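### The exit interview in Section 5.4.3 is worded too narrowly, and a dosed subject who leaves isolation before the diary card is issued has no planned recording for the rest of the 7-day safety window

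*Protocol*

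**What the plan says.** For premature withdrawal of any kind, the first bullet of Protocol Section 5.4.3 asks for an interview about "any reaction or AE (serious or non-serious) during the period one month after any study vaccination that has led to the withdrawal". The second bullet asks for a best effort to complete the Day 28 or Day 56 evaluations.

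The primary outcome in Section 3.2.1 is wider. It includes solicited reactions through 7 days and "All other adverse events (including unsolicited events) occurring during the 7 days following any dose". Section 9.2.2 states: "All solicited and unsolicited AEs occurring during the study will be assessed and recorded".

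The diary card is a Day 7 procedure after dose one (Section 7.2.8): "Subjects will be given a diary card in which they will be asked to record any local and/or systemic reactions". The second card is a Day 35 procedure (Section 7.2.17). For a subject who withdraws consent in the unit after dosing, Section 5.4.2.5 says "the subject will be requested to complete evaluations for that day and to complete either Day 28 or Day 56 evaluations, as applicable" and mentions no diary. It mentions one only for a subject who withdraws after discharge, who is asked to return it.

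**The concern.** Describing safety is the only primary objective, and the trial is small. Two features limit what is collected from a subject who leaves early.

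First, a site that follows the interview bullet to the letter asks only about events that caused the exit. Whether the question is asked then depends on the event itself.

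Second, Section 9.2.1.2 solicits local and systemic reactions while subjects are in the unit, and the diary takes over only from planned discharge. A subject who leaves in between falls under neither. Section 5.4.2.5 does foresee this period, since it advises the leaver to avoid close contact until 7 days after dosing, but it arranges no safety recording for those days.

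At stake is the completeness of the non-serious reaction and AE counts within 7 days of each dose.

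**Working it through.** **No planned figure to reproduce.** Section 11.1 states that no sample size is calculated, and the protocol gives no withdrawal rate. The check is therefore a comparison of passages, followed by the weight of one subject.

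**Step 1. What covers each period for a dosed subject who leaves the unit on Day 3 (example)**

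| Period | Planned recording | Source |
|---|---|---|
| Day 0 to exit | Interviews morning and afternoon and a physical examination on each day after dosing; that day's evaluations requested on withdrawal of consent | 7.2.1 to 7.2.4, 5.4.2.5 |
| Exit to Day 7 | None: reactions are solicited only in the unit, and the card is not issued until Day 7 | 9.2.1.2, 7.2.8 |
| Day 28 | Open question to "inquire about any new medical events since medical histories were last updated", if the subject attends | 5.4.3, 7.2.10 |

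The pattern after dose two is the same, with Day 35 and Day 56 in place of Day 7 and Day 28. The fallback visit falls 28 − 7 = 21 days, or 56 − 35 = 21 days, after the window closes, and an early leaver has no diary to review at it.

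**Step 2. Who is exposed.** A subject who withdraws after planned discharge has reached Day 7 or Day 35 and holds a card. A dosed subject in isolation may be withdrawn by the investigator only for a reaction thought to threaten well-being, with treatment or transfer (5.4.3), and withdrawals for an AE get follow-up visits (5.4.2.6). The exposed group is mainly subjects who leave the unit by choice before Day 7 or Day 35.

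**Step 3. Weight of one subject.** Arm sizes from Section 4: vaccine 9 + 21 = 30; placebo 3 + 7 = 10. One unknown outcome can move a proportion by up to 1/30 = 3.3 points in the vaccine arm or 1/10 = 10 points in the placebo arm.

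**Step 4. Range under assumed numbers.** Let x be observed events and w the leavers of unknown status. Section 11.3.1 calls for exact 95% intervals; Clopper-Pearson is used here: lower limit = Beta quantile (0.025; x, n − x + 1), upper limit = Beta quantile (0.975; x + 1, n − x). Assumed for the vaccine arm: x = 3 and w = 1 to 3.

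| w | No leaver had the event | Observed subjects only | Every leaver had the event |
|---|---|---|---|
| 1 | 3/30 = 10.0% (2.1 to 26.5) | 3/29 = 10.3% (2.2 to 27.4) | 4/30 = 13.3% (3.8 to 30.7) |
| 2 | 3/30 = 10.0% (2.1 to 26.5) | 3/28 = 10.7% (2.3 to 28.2) | 5/30 = 16.7% (5.6 to 34.7) |
| 3 | 3/30 = 10.0% (2.1 to 26.5) | 3/27 = 11.1% (2.4 to 29.2) | 6/30 = 20.0% (7.7 to 38.6) |

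In the placebo arm with x = 1 and w = 1, the range runs from 1/10 = 10% (0.3 to 44.5) to 2/10 = 20% (2.5 to 55.6). These are bounds on what is unknown, not estimates of bias. With w = 0 there is no effect.

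**The case against.** The strongest reply is that the exit interview is only one of several routes.

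- Events before exit are recorded by the in-unit interviews and same-day evaluations. The next sentence of the same bullet has the investigator assess any event the subject reports, and the Day 28 and Day 56 evaluations include an open enquiry. This stands: it would be wrong to say that only events causing the exit are ever asked about.
- SAEs within one month must be reported in every case (9.3.1). This stands, and it confines the point to non-serious events.
- The 7-day categories are defined by staff observation or report to staff, not by diary. This is true, but no staff contact is scheduled between an early exit and Day 28 or Day 56.
- Section 8.1.2 has symptoms entered on the diary card after discharge until participation ends, and Section 5.4.3 promises an SOP for exits from the unit. The SOP, which is not shown, may arrange more. The protocol itself has no step that hands a card to an early leaver, whose participation ends at withdrawal.
- The limiting clause could be read as attaching to something other than the reaction. That ambiguity is itself a reason to remove it.

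A reader might go further and infer that unrecorded events are counted as absent, because Section 11.2 says "All primary safety descriptions and summaries will be performed on an intention-to-treat basis", so that true events would be reported as zero. The protocol does not say so. Section 9.2.1.2 requires absence to be noted and graded zero, and Section 15.2 requires missing data to be explained, so a blank is not a zero. How incomplete windows are analysed may properly be left to the analysis plan.

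A reader might also see a conflict between one month in the interview and 4 weeks in the SAE outcome. A month is at least 28 days and contains that window, so nothing is lost.

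**Conclusion.** The point holds as a gap in data collection, not as a demonstrated bias. The interview wording is narrower than both the primary outcome and the duty to record all AEs. For a dosed subject who leaves isolation early, non-serious reactions between exit and the end of the 7-day window may be under-ascertained, above all if the Day 28 or Day 56 evaluation does not take place.

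The size cannot be fixed from the protocol. It rests on how many subjects leave early, whether they then have a non-serious event, and whether they return and recall it. The exposed group is probably small. The change is worth making because it is nearly free and concerns the sole primary objective.

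**What to change.** 1. In the first bullet of Section 5.4.3, remove the limiting clause and have the investigator ask about any reaction or AE since the last dose, whether or not it led to the withdrawal.
2. In Sections 5.4.2.5 and 5.4.3, have the existing diary card given, with its instructions, to every dosed subject at any exit from the isolation unit and returned at the Day 28 or Day 56 evaluation.

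The cost is two sentences and earlier use of an existing form, with no added visits or subjects. The card gains nothing for a subject who does not return it. It also arrives after the Safety Monitoring Committee review that the Trial Scheme places on or soon after Days 8 and 36. It improves the final safety description, not that review.

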## 5.5 Termination of the Trial

### 5.5.1 Termination According to the Protocol

Termination of the trial according to the protocol is the date of the last visit of the last subject participating in the trial, according to the trial scheme. Of note, each sub-cohort will have a different termination date for that sub-cohort.

### 5.5.2 Suspension and/or Premature Termination of the Trial

The trial might be suspended at any time by the Sponsor, PVS, the Russian Ministry of Health, the SMC, any ethical review committee overseeing this study, or by the investigator for any safety concern. This includes, for example, and without limitation, an SAE resulting in death, an unexpectedly high number of persons shedding virus after receipt of any dose, an unusually high rate of SAEs, or an unexpectedly early onset of substantial seasonal influenza virus circulation in the surrounding community. PVS may suspend the study in the event that study conduct is found to be below Good Clinical Practice (GCP) standards.

In the event of the appearance of new data that indicate an increased level of risk to participating subjects, the clinical trial will be suspended until the Sponsor, PVS, the Russian Ministry of Health, the SMC, and all ethical review committees have reviewed relevant data and agreed that the trial may proceed.

## **6 Study Products**

### **6.1 Study Product Descriptions**

#### **6.1.1 Study Vaccine**

Study vaccine for this trial is a cold-adapted, live attenuated monovalent A/17/mallard/Netherlands/00/95(H7N3) influenza vaccine. The virus strain in this vaccine was constructed in the laboratories of IEM by classical reassortment of A/mallard/Netherlands/12/00(H7N3) virus with a cold-adapted temperature sensitive A/Leningrad/134/17/57(H2N2) virus master donor strain in developing chicken embryos. The 6:2 genomic reassortant was characterized for acceptable phenotype and genotype [presence of cold-adapted, temperature sensitive, HA, and NA markers], with genetic sequencing used to confirm the molecular basis of the attenuated phenotype. The developed vaccine strain was transferred to Microgen, to produce a bulk lot of vaccine for use in preclinical immunogenicity and challenge studies and for use in clinical trials. Manufactured vaccine was obtained from virus-containing allantoic fluid of chicken embryos. Microgen has transferred the manufactured vaccine back to IEM where it has been securely stored.

LAIV H7N3 is a lyophilizate (a light yellow-colored amorphous mass) of live attenuated influenza virus for the preparation of a solution for intranasal introduction. The active component is the vaccine strain A/17/Mallard/Netherlands/00/95(H7N3) virus obtained from the allantoic fluid of chicken embryos. LAIV H7N3 is supplied lyophilized in single-dose ampoules [specific activity of the vaccine is not less than 7.5 log EID50/0.5 ml dose]. The lyophilizate also contains the following stabilizers: sucrose, lactose, glycine, sodium glutamate, tris (hydroxymethyl) amino-methane, sodium chloride, and gelatin.

